### Participant retention

#### Retention of TH clusters

Upon enrollment, TH were assigned a unique identification number, and the study team collected detailed locator information, including contact information for the TH, multiple designated contact persons, and detailed residence information for all TH who provided informed consent to participate in the trial. We will provide contact information for our study team members to the TH and will remain available to answer any questions that arise. In the 2 weeks leading up to the biannual TH refresher trainings, an RA will call each participating TH to remind them of the upcoming training time and location. RAs will also send a reminder text message the day before the refresher trainings. If a TH is not reachable by phone, RAs will make site visits to remind the TH in person.

#### Retention of PLWH participants

Upon enrollment, study participants will be assigned a unique identification number and will complete a detailed locator information form that includes contact information for the participant, multiple participant-designated contact persons, and detailed residence and workplace information. These designated contact persons will be peers or family members whom the study team can contact if the participant is not reachable for follow-up through other means. Study staff will contact participating PLWH via mobile phone following enrollment to assess for (re)linkage to care within 7 days of study enrollment. For participants who cannot be reached by phone during the initial follow-up, study staff will call a backup contact to inquire about the participant’s whereabouts (taking care not to mention HIV status or the purpose of the study). If participants are not reachable via their designated contacts, study staff will invoke the assistance of participants’ TH to help locate the individual, as TH are often in regular contact with their clients. Participants will be notified 2 weeks by phone call prior to the study staff’s 12- and 24-month visits and receive a reminder the day before via text message.

#### Retention of HIV clinic staff and liaisons

Upon enrollment, clinic staff and liaisons will be assigned a unique identification number, and we will collect contact information for each clinician, including mobile number and workplace information. The study staff will contact clinicians 2 weeks ahead of schedule to arrange interviews at specific times and in private locations convenient for the clinicians. If clinicians are unavailable by phone, research assistants will visit their workplaces to schedule their interviews.

#### Retention of policymakers

A sample of seven health officials in the Ministry of Health AIDS Control Office or District Health Offices will be invited to participate in three individual interviews, the first at the time of the study launch, then again after 12 and 24 months. Upon enrollment, each health official will be assigned a unique identification number, and we will collect contact information for each official, including mobile number and workplace information. RAs will contact officials 2 weeks ahead of schedule to arrange interviews at specific times and private locations convenient for the officials.

### Data collection and management

#### Quantitative data collection

Study staff and clinical liaisons will collect data on the effectiveness of the intervention. PLWH participants will receive an in-person visit from a member of the study team to complete a plasma blood draw for the HIV-1 RNA viral load assay at baseline, 12 months, and 24 months, and a hair sample collection at 12 months following enrollment. All the data will be collected in private locations. Data regarding engagement with clinical care will be reported by liaisons or abstracted by the study team from clinic cards. All clinical data will be entered into a secure database (REDCap) hosted by Weill Cornell Medical College.

The study team will collect quantitative data on intervention implementation. All TH (*n* = 44) and PLWH (*n* = 650) will complete survey items administered by the study staff. Translated questions will be loaded onto encrypted study tablets, and responses will be entered directly into REDCap. RAs will read items aloud to accommodate participants with limited literacy. The Theoretical Framework of Acceptability (TFA) scale will be administered at baseline and 12 months [62–64]. Fidelity will be measured via quarterly structured observations, with intervention TH to be scored by a member of the study team according to core elements of the intervention curriculum: (1) facilitating rapid linkage to HIV care and (2) delivery of psychosocial support using one or more key elements (ART adherence, healthy living, HIV status disclosure, identifying mental health symptoms) [65]. Adoption will be quantified as the number of eligible TH invited who agree to participate as cluster sites. Reasons for refusal to participate will also be documented. Finally, maintenance will be assessed 12 months after training and support for the intervention has ended. We will quantify the maintenance of viral suppression via HIV-1 viral load measurements from PLWH in both study arms 24 months after enrollment.

Additional participant data collected at enrollment will include age, sex, income, education attained, religious affiliation, marital status, and history of HIV testing. PLWH quality of life will be measured using the Medical Outcomes Study-HIV Health Survey (MOS-HIV) [66]. PLWH, TH, and clinician HIV knowledge will be measured using the HIV Knowledge Questionnaire (HIV-KQ-18) [60]. PLWH social support will be measured using the Duke-UNC Functional Social Support Questionnaire (FSSQ) [67]. PLWH self-efficacy will be measured by the HIV-ASES scale [57]. PLWH, TH, and clinician stigma will be measured using the HIV-Stigma Scale [58]. Furthermore, PLWH stigma will also be measured using the HIV Stigma Mechanisms Scale (HIV-SMS), and TH and clinician stigma will be measured using the HIV Stigma and Discrimination Scale [59, 68].

#### Qualitative data collection

Overall, 69 participants will be invited for qualitative interviews (*n* = 22 intervention TH, *n* = 20 intervention PLWH, *n* = 20 HIV clinicians, and 7 health officials). TH, PLWH, HIV clinicians, and health officials will participate in three interviews (at baseline, 12 months after study initiation, and 24 months after study initiation). Participants will be purposively sampled to share first-hand knowledge about their experiences with intervention [14]. We will select interview participants to ensure representation by sex, age, clinical position (for HIV clinicians), geographic distribution, and viral load (for PLWH).

The interviews will be guided by CFIR as a framework (Table 2), conducted in private locations for ~ 60 min, and based on an interview guide to allow for the exploration of novel topics and the elicitation of information-rich data [28–31]. The interview guides will be composed in English, translated into Runyankole, and translated back to English to ensure the integrity of meaning. Interviews in Runyankole will be conducted by trained members of the Ugandan qualitative team, audio-recorded and transcribed and translated into English by the interviewer. Transcripts will be spot-checked against audio recordings by the Qualitative Data Coordinator and the Ugandan PI (both fluent in Runyankole and English) to ensure translation validity and integrity.

### Data management and confidentiality

All quantitative study data will be collected using Android tablets and uploaded daily into the REDCap data management system, which is compliant with Good Clinical Practice and 21 CFR Part 11 regulations [69, 70]. All de-identified qualitative study data will be uploaded to a secure OneDrive, which is password-protected and compliant with NIH data storage requirements.

Informed consent documents will be retained in locked filing cabinets and storerooms, accessible only to senior investigators and designated study staff. All questionnaires and samples are de-identified at the time of collection. The lists linking study numbers to names are kept separately on a password-protected computer, accessible only to the PI, Ugandan PI, and project manager. Standard service-related clinical and HIV counseling records and consents are kept in secure files in locked offices, accessed only by approved personnel. Clinicians and counselors have received training on the need to maintain complete confidentiality of client data. All computerized databases and files will contain only study ID numbers.

### Data analysis

#### Interim analyses

Interim analysis will be conducted after 50% of the study participants have completed their 12-month evaluations, with the following objectives: (1) examine the validity of assumptions made for estimating sample size; (2) decide whether early termination of the trial is warranted due to clear efficacy or lack thereof; and (3) determine whether there are unanticipated reasons for early trial termination or modification. No stopping rules have been predefined for this trial, given that the research procedures are minimally invasive and present low risks to the study participants.

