#### Statistical methods for primary outcomes

The primary outcome of the trial is viral suppression, defined as a plasma HIV-1 RNA concentration < 200 copies/mL [38]. An intent-to-treat analysis will be used to assess the primary outcome at 12 months among PLWH in the intervention group compared with the control group. A mixed effects logistic regression model—with individual PLWH in level 1 nested within TH in level 2—will be applied to determine if the intervention increases the relative risk of viral load suppression compared with the control. We will conduct additional analyses to account for the heterogeneous effect of individual PLWH-level parameters on viral suppression in the mixed effects logistic regression model. The individual PLWH-level parameters to be accounted for may include newly diagnosed patients with HIV at enrollment vs. previously diagnosed patients; demographic variables such as age, sex, and socioeconomic status; and survey measures such as social support and HIV stigma. We will also apply an estimand framework analysis to consider the impact of intercurrent events on the primary outcome of HIV viral suppression. *p* < 0.05 will considered to indicate statistical significance in this primary analysis. Participants lost to follow-up will be considered virally unsuppressed for the primary outcome analysis.

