### Oversight and monitoring

The study has an Administrative Core, Steering Committee, and Data Safety and Monitoring Board (DSMB). The Administrative Core comprises the study principal investigators, a full-time Ugandan project manager, and a full-time US research coordinator. Together, they oversee trial activities and regulatory requirements and coordinate team meetings. The Steering Committee comprises principal investigators, coinvestigators, a project manager, quantitative and qualitative data managers, and two Ugandan research assistants. This committee ensures adherence to the study protocol and standard operating procedures to achieve the stated research goals.

The three-person DSMB is an independent external monitoring committee that includes a biostatistician, clinical trialist, and HIV clinician. The DSMB met prior to study initiation to review the consent forms and protocol and will meet every 6 months throughout the study period or more frequently as needed. Prior to their meeting, the DSMB will receive open reports of study progress and all adverse events (please see below), including breaches of confidentiality, stigma, and social harm. After the 325th participant has been enrolled, the DSMB will be presented with interim analysis results and decide whether to terminate, modify, or continue the trial.

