### Dissemination plans

The trial has been registered on ClinicalTrials.gov, and the record will be updated at least once per year and within 30 days of a change to applicable sections of the ClinicalTrials.gov record. Final trial results will be posted on ClinicalTrials.gov no later than 1 year after the study’s primary completion date. Preliminary results will be presented twice per year to our ten-person traditional healer Community Advisory Board and to the local academic community at the annual Mbarara University of Science and Technology Research Dissemination Conference. In addition, we will organize annual dissemination meetings with officers from the Ugandan Ministry of Health AIDS Control and Community Health Divisions, along with stakeholders from civil society organizations. Scientific abstracts will be submitted to international and domestic conferences, and trial results will be submitted for publication in peer-reviewed journals, with all publications as open access.

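### The interim look may stop the trial for efficacy with no stated criterion and no allowance in the final test, and the protocol gives it two conflicting triggers about a year apart

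*Protocol article*

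**What the plan says.** Everything below is in the Protocol article.

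- **Interim analyses, timing:** "Interim analysis will be conducted after 50% of the study participants have completed their 12-month evaluations".
- **Interim analyses, purpose:** three aims are listed. The first is to check the sample-size assumptions. The second is to "decide whether early termination of the trial is warranted due to clear efficacy or lack thereof". The third concerns unanticipated reasons to stop or modify the trial.
- **Interim analyses, rule:** "No stopping rules have been predefined for this trial". The only reason offered is that what is done to participants is barely invasive and carries little risk.
- **Statistical methods for primary outcomes:** p < 0.05 "will considered to indicate statistical significance in this primary analysis". The interim look is not mentioned there.
- **Oversight and monitoring:** "After the 325th participant has been enrolled, the DSMB will be presented with interim analysis results", at which point the board decides to terminate, modify or continue.

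The target is 650 participants (Sample size), so 325 is half of those enrolled. The primary outcome is measured 12 months after enrollment (Effectiveness outcomes).

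**The concern.** A look that can end the trial for benefit is a second chance to declare success. Unless its threshold is fixed in advance and counted in the final test, the false-positive rate of the primary comparison is unknown. The reason given for having no rule, low risk to participants, bears on stopping for harm. It does not bear on stopping for benefit.

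This is more than detail left to an analysis plan or a board charter, because the article says that no rule has been predefined.

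The trigger matters for the same decision. If the look follows the 325th enrollment, the board must judge efficacy or futility on very few 12-month results. If it follows the 325th completed evaluation, recruitment is nearly or fully over, and the check of the sample-size assumptions has little left to act on.

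**Working it through.** The protocol gives no error rate for the two looks, so there is no figure of its own to reproduce.

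**1. Overall type I error**

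Assumptions: two-sided tests (sidedness is not stated), one interim and one final look, and test statistics that are bivariate normal under the null with correlation √t, where t is the information fraction at the interim. The final test is at 0.05 (critical value 1.96).

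Overall error = P(|Z1| > c1 or |Z2| > 1.96). At t = 0.5:

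| Interim criterion | Overall error |
|---|---|
| p < 0.001 | 0.0502 |
| p < 0.01 | 0.0546 |
| p < 0.05 | 0.0831 |

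**2. Effect of clustering on t**

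Half the participants is half the information only if the intracluster correlation (ICC) is zero. Suppose all 44 clusters are half filled at the look, with m = 650/44 = 14.8 per cluster at the end. Then

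t = 0.5 × [1 + (m − 1)·ICC] / [1 + (m/2 − 1)·ICC].

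The article gives no ICC, so a range is assumed. The top value is back-calculated:

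- 60% versus 80% at 85% power needs 93 per arm without clustering.
- After 10% loss, 325 × 0.9 = 292.5 per arm remain, so the implied design effect is 292.5/93 = 3.15.
- With 292.5/22 = 13.3 analysed per cluster, ICC = (3.15 − 1)/(13.3 − 1) ≈ 0.17.

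| Assumed ICC | t | Overall error, 0.05 at both looks |
|---|---|---|
| 0 | 0.50 | 8.3% |
| 0.01 | 0.54 | 8.2% |
| 0.05 | 0.64 | 7.8% |
| 0.17 | 0.80 | 7.1% |

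**3. Timing of the two triggers**

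Trial status gives recruitment from 7 July 2023 to about 30 July 2025, which is 754 days. Accrual is modelled as N(day) = 650 × (day/754)^g. Here g = 1 is uniform (650/754 = 0.86 per day), g < 1 is front-loaded and g > 1 is back-loaded. The range examined is g = 0.5 to 3.

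*Enrollment trigger, g = 1.* The 325th enrollment falls on day 377, about 18 July 2024. Those who have reached 12 months number 0.862 × (377 − 365) ≈ 10, or about 9 after 10% loss. With 9.3 participants split equally, and ignoring clustering, the standard error of the difference is √[(0.24 + 0.16)/4.65] ≈ 0.29. That exceeds the 20-point effect the trial is designed to detect. Over g = 0.5 to 3, the number at 12 months runs from 0 to about 36.

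*Completion trigger, g = 1.*
- With no loss, day 377 + 365 = 742, about 18 July 2025. Enrolled by then: 0.862 × 742 ≈ 640.
- With 10% loss, the 325th completer is about the 361st enrolled (325/0.9), reached on day 419. Day 419 + 365 = 784, about 28 August 2025, when all 650 are enrolled.
- With strongly front-loaded accrual (g = 0.5), the look falls between January and February 2025, with about 557 (no loss) to 579 (10% loss) enrolled.

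The 12-month visit also has a window of up to 30 days, which is not added here. The triggers are therefore at least about 12 months apart.

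**4. Cost of a boundary**

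With an interim threshold of p < 0.001 at t = 0.5, a final level of 0.0498 gives exactly 0.05 overall. Leaving the final test at 0.05 gives 0.0502.

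**The case against.** - **The 8.3% is close to a worst case.** This stands. No section says that the interim test uses 0.05, and an efficacy result described as clear suggests something stricter. A reader might infer that the trial runs at 8.3%. The documents support only a range that starts at about 5.0%, and clustering lowers the top of it.
- **The triggers may not truly conflict.** The oversight sentence says the results come after the 325th enrollment. Literally, that is a lower bound which the later date also satisfies, and 325 may be shorthand for the 50% in the analysis section. This is possible. But the sentence names that enrollment as the marker for the board's decision, and no section reconciles the two. A reader should not conclude that the look will certainly be almost empty of outcome data. It would be so only if the enrollment wording governs.
- **The timing figures depend on accrual shape and loss.** This stands, and ranges are given for that reason.
- **There are safeguards.** The monitoring board is independent and includes a biostatistician, the statistician is blinded during analysis, and there is only one look. These make a careless stop less likely, but they do not define the error rate.
- **Dissemination plans.** A reader might infer from "Preliminary results will be presented twice per year to our ten-person traditional healer Community Advisory Board" that results by arm reach healers while the trial is running. The documents do not support this: they do not say that these results are by arm or concern viral load, and implementation data are also collected throughout.

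**Conclusion.** The concern holds in two parts. First, stopping for efficacy is an explicit aim, the protocol states that no rule exists, and the final test makes no allowance. The overall two-sided error is therefore undefined, lying between about 5.0% and 8.3%. If 0.05 were used at both looks, it would be about 7.1% to 8.2% for assumed ICCs of 0.17 to 0.01. Second, the two sections tie the look to events at least about 12 months apart. At the earlier one, 0 to about 36 participants would have reached 12 months (about 10 under uniform accrual), too few for any efficacy or futility decision. At the later one, under uniform accrual, about 640 to 650 would be enrolled, so a sample-size check could do little to adjust enrollment.

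These figures rest on two-sided testing, a single interim look, the assumed ICCs, evenly filled clusters and the accrual shapes shown. The lack of a criterion and the difference in wording do not depend on them.

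**What to change.** 1. State one trigger in both Interim analyses and Oversight and monitoring: 325 participants with a completed 12-month primary outcome evaluation.
2. Then choose one of two courses before any comparative interim data are seen:
   - prespecify an efficacy boundary, tested with the clustered primary model (for example Haybittle-Peto, interim p < 0.001 and final level about 0.0498), with a non-binding futility guide; or
   - state that the look cannot stop the trial for efficacy, and leave the final test at 0.05.
3. If the sample-size assumptions are to be checked in time to act on them, do so earlier, on data pooled over arms. The completion trigger comes too late for that aim.

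The cost is a short amendment and, under the first course, a final level of about 0.0498 in place of 0.05. No extra participants are needed.

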#### Statistical methods for primary outcomes

The primary outcome of the trial is viral suppression, defined as a plasma HIV-1 RNA concentration < 200 copies/mL [38]. An intent-to-treat analysis will be used to assess the primary outcome at 12 months among PLWH in the intervention group compared with the control group. A mixed effects logistic regression model—with individual PLWH in level 1 nested within TH in level 2—will be applied to determine if the intervention increases the relative risk of viral load suppression compared with the control. We will conduct additional analyses to account for the heterogeneous effect of individual PLWH-level parameters on viral suppression in the mixed effects logistic regression model. The individual PLWH-level parameters to be accounted for may include newly diagnosed patients with HIV at enrollment vs. previously diagnosed patients; demographic variables such as age, sex, and socioeconomic status; and survey measures such as social support and HIV stigma. We will also apply an estimand framework analysis to consider the impact of intercurrent events on the primary outcome of HIV viral suppression. *p* < 0.05 will considered to indicate statistical significance in this primary analysis. Participants lost to follow-up will be considered virally unsuppressed for the primary outcome analysis.

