### Evidence-based program selection and adaptation

Prior to study initiation, the Omuyambi study team identified an evidence-based lay counseling program that could be adapted for TH delivery. We selected the Patient Advocate Program to adapt to rural Ugandan healers. This community health worker-delivered intervention was developed for PLWH who defaulted from care and assists in (re)linking PLWH to HIV care, supporting ART (re)initiation and adherence through medication counseling, and facilitating retention in care through the provision of individual psychosocial support. A multicenter cohort study among ~ 67,000 PLWH at 57 sites in South Africa showed that the Patient Advocate Program improved viral suppression 8 years after ART initiation compared with routine care (88.6 vs. 80.6%, adjusted RR = 1.53) [32, 33]. This evidence-based program required adaptation for our setting, as it was developed in a semiurban South African context with a robust force of community health workers, unlike rural Uganda. We adapted the program for TH as they are accessible and trusted lay providers in rural Ugandan communities where health facilities are scarcer, literacy is lower, and baseline viral suppression is poorer than the original intervention location. Details of the adaptation process and pilot testing of the TH-delivered program can be found in Sundararajan et al. [34].

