### Sample size

Study power calculations are based on the primary hypothesis that the intervention will improve viral suppression by 20% using standardized methods for cluster randomized trials [51]. Based on population-level data from the Ugandan Ministry of Health, we assume that the proportion of PLWH achieving the primary outcome of viral suppression will be 60% in the control arm versus 80% in the intervention arm [3]. The results of prior community-based and psychosocial HIV support interventions were used to inform this estimated effect size [32, 52, 53]. To ensure 85% power to detect a difference of ≥ 20% in viral suppression between arms and assuming a 10% loss-to-follow-up rate, we will enroll a minimum of 16 PLWH in each cluster. The target sample size is 650 PLWH, with 325 PLWH in each arm. Forty-four TH will be enrolled as cluster sites, with 22 in each study arm.

As part of the implementation evaluation, we will purposively recruit 20 PLWH, 20 HIV clinicians, and 7 policymakers for participation. The sample size of 20 HIV clinicians is based on prior research showing that thematic and conceptual data saturation is obtained after 12–16 interviews have been conducted within a subgroup [54, 55]. Due to the limited number of policymakers, 7 interviews will be conducted to understand local and national government priorities and implementation context.

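### The primary mixed logistic model is said to assess a relative risk, but its arm effect is a healer-conditional odds ratio and no step from one to the other is named

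*Protocol article*

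**What the plan says.** Under *Statistical methods for primary outcomes* the protocol article names one primary model: "A mixed effects logistic regression model—with individual PLWH in level 1 nested within TH in level 2—will be applied". It gives the purpose in the same sentence: the model "will be applied to determine if the intervention increases the relative risk of viral load suppression compared with the control". The words odds ratio do not occur in the article. No log link, Poisson model, standardisation or other conversion is mentioned. The same section counts participants lost to follow-up as unsuppressed.

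Under *Sample size* the effect is given as two proportions, "60% in the control arm versus 80% in the intervention arm", which is an absolute difference of 20 percentage points, with an allowance of 10% for loss to follow-up. No intracluster correlation is printed.

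Under *Evidence-based program selection and adaptation*, the South African cohort behind the parent programme is reported to have "improved viral suppression 8 years after ART initiation compared with routine care (88.6 vs. 80.6%, adjusted RR" = 1.53).

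**The concern.** A random-intercept logistic model works on the log-odds scale. Its arm coefficient compares the odds of suppression between arms for participants who share the same value of the healer effect. That is not a relative risk. The usual excuse, that an odds ratio approximates a relative risk when the outcome is rare, is not available when most participants are expected to be suppressed.

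An analyst following the text literally could exponentiate the coefficient and report it under the label the protocol supplies. A second analyst could standardise the model predictions and report a true relative risk. From the same data they would publish very different numbers under one name. *Dissemination plans* sends results to Ministry of Health officers and civil society organisations, who would reasonably read a relative risk as a multiplier of the proportion suppressed.

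**Working it through.** **Inputs.** Control 0.60 and intervention 0.80 (*Sample size*). Loss to follow-up 10% (*Sample size*), with losses counted as unsuppressed (*Statistical methods for primary outcomes*). The ICC is not given, so a latent-scale range of 0 to 0.30 is assumed.

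**Step 1: the plan's own contrast.** The risk difference is 0.80 − 0.60 = 0.20, which matches the 20 points stated.

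**Step 2: relative risk and marginal odds ratio at the design rates.**
- Relative risk = 0.80/0.60 = 1.33.
- Marginal odds ratio = (0.80/0.20)/(0.60/0.40) = 4.00/1.50 = 2.67.
- Odds ratio divided by relative risk = 2.67/1.33 = 2.00.

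Read as a relative risk, 2.67 on a 60% base would mean 2.67 × 60% = 160% suppressed, so the two labels are not interchangeable here.

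**Step 3: what the named model estimates.** The marginal rates were held at 0.60 and 0.80. The random-intercept variance was set to [ICC/(1 − ICC)] × π²/3, and the two conditional intercepts were solved by numerical integration over the random effect. The cluster-specific odds ratio is the exponential of their difference.

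**Step 4: allow for losses.** If 60% and 80% describe participants who complete, and 10% are lost in each arm and counted as unsuppressed, the rates become 0.9 × 0.60 = 0.54 and 0.9 × 0.80 = 0.72. The relative risk is still 0.72/0.54 = 1.33. The marginal odds ratio is (0.72/0.28)/(0.54/0.46) = 2.19, which is 1.64 times the relative risk. Step 3 was repeated at these rates.

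| Assumed latent ICC | Cluster-specific OR, 60% vs 80% | Multiple of RR | Cluster-specific OR, 54% vs 72% | Multiple of RR |
|---|---|---|---|---|
| 0 | 2.67 | 2.00 | 2.19 | 1.64 |
| 0.05 | 2.76 | 2.07 | 2.26 | 1.69 |
| 0.10 | 2.86 | 2.15 | 2.33 | 1.75 |
| 0.20 | 3.10 | 2.32 | 2.50 | 1.87 |
| 0.30 | 3.40 | 2.55 | 2.70 | 2.03 |

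**Step 5: the quoted 1.53.** From the printed percentages, the ratio of suppression is 0.886/0.806 = 1.10, and no ratio against 80.6% can exceed 1/0.806 = 1.24. A suppression ratio of 1.53 would need a reference risk of at most 1/1.53 = 65.4%. Other crude readings do not give 1.53 either: the odds ratio is (0.886/0.114)/(0.806/0.194) = 1.87, and the ratio of non-suppression is 0.194/0.114 = 1.70.

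**The case against.** The strongest reply is that the sentence gives the purpose of the model and does not promise to publish an exponentiated coefficient as a relative risk. A mixed logistic model can yield a relative risk by standardisation, and such a step is often left to an analysis plan, which is not shown here. This stands as far as the harm is concerned: overstatement is conditional on how the result is reported. It does not remove the fault, because the article itself assigns a relative risk to a model whose direct output is something else.

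Four stronger readings are tempting and are not supported.

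- *The primary test is invalid.* It is not. An odds ratio of 1, a relative risk of 1 and a difference of 0 coincide, so the decision at p < 0.05 is untouched.
- *Sizing on a difference and testing with a logistic model is an error.* It is common and acceptable. The 20 points is a power assumption.
- *The model's odds ratio is exactly twice the relative risk.* That figure belongs to the marginal odds ratio at 60% versus 80%. The cluster-specific multiple depends on an ICC that the article does not state and on how losses enter the rates.
- *The 1.53 is an odds ratio under the wrong name, and the effect size rests on it.* The estimate is adjusted, the adjustment status of the two percentages is not given, and the crude odds ratio is 1.87. One of the two references for that figure is among the three cited for the effect size, but the sizing uses 60% and 80%, not 1.53.

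**Conclusion.** The point holds as a mismatch between the named effect measure and the named model. The relative risk at the design rates is 1.33 under either treatment of losses. The quantity the model directly estimates would be 2.0 to 2.55 times that at 60% versus 80%, or 1.64 to 2.03 times that at 54% versus 72%. These ranges assume a normal random intercept, a latent-scale ICC between 0 and 0.30 and, for the second range, equal 10% loss in both arms. In every case examined the gap is too large to ignore. The consequence concerns the size and interpretation of the reported benefit, and arises only if the coefficient is reported under the stated label.

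On the background figure, the documents support only this: 1.53 cannot be obtained from 88.6% and 80.6% as a ratio of suppression, and what it measures cannot be settled from the article.

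**What to change.** Keep the mixed effects logistic model for the hypothesis test. Add to *Statistical methods for primary outcomes* that the relative risk will be obtained from the fitted model by marginal standardisation: predict each participant's probability of suppression under both arms, integrate over the healer random effect, average over the trial population, and take the ratio. Report the risk difference from the same predictions alongside it, since the trial is sized on 60% versus 80%. Give 95% confidence intervals that respect clustering, for example from a bootstrap that resamples healers or from the delta method. Label any exponentiated coefficient a cluster-specific odds ratio. Making the risk difference primary or moving to a modified Poisson GEE would also be workable, but is a preference and is not needed to cure the fault.

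The cost is a clause of text, a few lines of code and a less striking ratio. Design, data collection and sample size are unchanged. The wording is best settled before the arms are compared at the interim analysis.

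Separately, check the adjusted RR of 1.53 against its source and state which outcome and which measure it refers to.
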